## Study Protocol

The original study protocol was written in Dutch. This document was translated to English for publication using Microsoft Copilot (GPT-5) on November 4th 2025.

Microsoft. Copilot (GPT-5) [Large language model]. Microsoft; 2025.

Available from: <https://copilot.microsoft.com>

### Study Product

Tensiofytol®

# 1. Protocol Summary

## 1.1 Protocol Synopsis

### **Primary and Secondary Objectives and Endpoints**

|                    | Objective                                       | Endpoint                                                                                                                        |
|--------------------|--------------------------------------------------------|----------------------------------------------------------------------------------------------------------------------------------------|
| Primary     | Decrease in blood pressure                             | Systolic blood pressure*                                                                                                               |
| Secondary   | Decrease in blood pressure                             | Systolic blood pressure after 4 weeks*                                                                                                 |
|                    | Decrease in blood pressure                             | Diastolic blood pressure*                                                                                                              |
|                    | Change in markers of oxidative stress                  | oxLDL*, MDA*, GSH*                                                                                                                     |
|                    | Change in lipid profile                                | Total cholesterol*, HDL*, LDL*, non-HDL*, Remnant cholesterol*, Triglycerides*, Apolipoprotein A1*, Apolipoprotein B*, Lipoprotein(a)* |
|                    | Evaluation of side effects                             | Side effects                                                                                                                           |
| Exploratory | Change in parameters linked to metabolic syndrome.     | Fasted glucose*, Hemoglobin A1c*, fasted insulin*, fasted C-peptide*                                                                   |
|                    | Change in parameters linked to metabolic syndrome.     | BMI* en waist circumference*                                                                                                           |
|                    | Change in parameters linked to cardiovascular diseases | Hemoglobin*, Creatinine*, CRP-US*, Homocysteine*                                                                                       |

\* This always refers to the absolute difference compared to the baseline value after 8–9 weeks, unless stated otherwise

### **Study Design**

Randomised, placebo-controlled, double-blind study investigating the effect, tolerance, and efficacy of Tensiofytol® compared to a placebo in individuals aged 18 years or older and younger than 78 years with elevated blood pressure.

### **Number of Arms**

2 groups: Tensiofytol® and placebo

### **Blinding**

Double-blind study; participants and researchers are unaware of the study group assignments.

### **Number of Participants**

56 participants; 28 per group

## 1.2 Trial Schema

[figure not shown]

## 1.3 Schedule of Activities

| Screening                                                                                                                                                                                                                                                                                                                                                                              | Intermediate blood pressure measurement                                                                     | End Visit                                                                                                                                                                                                                                                                                                                                         |
|----------------------------------------------------------------------------------------------------------------------------------------------------------------------------------------------------------------------------------------------------------------------------------------------------------------------------------------------------------------------------------------|-------------------------------------------------------------------------------------------------------------|---------------------------------------------------------------------------------------------------------------------------------------------------------------------------------------------------------------------------------------------------------------------------------------------------------------------------------------------------|
| Week 0                                                                                                                                                                                                                                                                                                                                                                                 | Week 4 after start treatment                                                                                | Week 8 – 9 after start treatment                                                                                                                                                                                                                                                                                                                  |
| 
 
Review and signing of Informed Consent Form
 
Complete contact form
 
Blood pressure measurement
 
Check inclusion and exclusion criteria
 
Complete Food Frequency Questionnaire
 
Complete start questionnaire
 
Measure weight, height, and waist circumference
 
Blood sampling
 
 | 
 
Blood pressure measurement
 
Adverse event inquiry
 
 | 
 
Blood pressure measurement
 
Complete Food Frequency Questionnaire
 
Complete end questionnaire
 
Measure weight and waist circumference
 
Unblinding
 
Provide book voucher and Tensiofytol® packaging if the participant received placebo during the study
 
 |

## 2. Introduction

### 2.1 Rationale

Cardiovascular diseases (CVD), such as stroke or heart attack, are among the leading causes of death worldwide, with 17.9 million deaths per year [1]. High blood pressure is the main risk factor for developing CVD. It is also an important risk factor for other conditions such as chronic kidney disease and dementia [2].

In pathological situations, such as hypertension, large amounts of reactive oxygen species (ROS) are released. If endogenous antioxidants cannot neutralise these, it leads to oxidative stress. Oxidative stress is closely involved in the development and progression of CVD [3].

Studies indicate elevated levels of malondialdehyde (MDA), 8-iso-prostaglandin, and oxidised LDL (oxLDL, a key marker of oxidative lipid damage) [4–6].

Individuals with a combination of CVD risk factors — such as abdominal obesity, dyslipidemia, high blood pressure, and glucose intolerance — are considered to have metabolic syndrome (MetS), which greatly increases their risk of developing CVD [7].

Preventing CVD is therefore extremely important. Lifestyle changes, such as dietary adjustments, physical activity, and smoking cessation, as well as medication, can help [8]. Due to the high prevalence of CVD, further research into antihypertensive and antioxidant therapies is needed.

Polyphenols in olive extract have antioxidant properties and may therefore be useful in combating oxidative stress [9]. Previous studies (including one by the NatuRAPT research group using a combination of olive extract and red yeast rice) have shown that olive extract can lower elevated blood pressure [10,11]. Additionally, olive polyphenols have a positive effect on cholesterol levels [12–14]. Several years ago, EFSA (European Food Safety Authority) approved a health claim (“protects LDL from oxidation”) for olive oil preparations related to a daily intake of 5 mg hydroxytyrosol [15,16]. Other studies have demonstrated an anti-hyperglycemic effect in individuals taking olive leaf extract for 12 weeks [17].

Olive polyphenols may therefore have a beneficial effect on various CVD risk factors.

In the current study, the effect of a standardised olive extract (Tensiofytol® – Tilman) will be investigated compared to placebo. Tensiofytol® is available over the counter, and the recommended daily dose contains 334 mg olive leaf dry extract and 106 mg olive fruit dry extract (*Olea europaea* L.; equivalent to 100 mg oleuropein and 20 mg hydroxytyrosol), divided over 2 capsules. For technical reasons, the same amount of product will be distributed over 3 capsules in this study.

## 2.2 Summary of Benefits and Risks

### **Benefit Summary**

The dietary supplement in this study may help lower blood pressure and maintain healthy blood pressure, which, according to current medical insights, benefits the heart and blood vessels. During the study, the participant will receive information about their cardiovascular health and blood pressure values. In addition, the participant supports scientific research aimed at improving the treatment of elevated blood pressure.

### **Risk Summary**

It cannot be guaranteed that the participant will personally gain direct benefit from participation. For example, the participant may be assigned to the placebo group, or it may turn out that the dietary supplement does not cause any change.

During the screening and final visit, blood samples will be taken. Blood sampling may cause minor discomfort, such as a small bruise. The blood draw will always be performed by a trained professional. The participant may experience side effects from the dietary supplement. There may also be risks and inconveniences that are currently unknown. During the study, participants will be asked about possible side effects. The participant may stop the study at any time, for example, if they experience discomfort from the supplement.

### 3. Trial Objectives and Endpoints

#### 3.1 Trial Objectives

This study primarily aims to determine whether administering a commercially available standardised olive extract (Tensiofytol®) to individuals with elevated blood pressure can lead to a significant short-term reduction in blood pressure.

In addition, the study will examine whether the extract can cause changes in markers of oxidative stress and the lipid profile. The tolerance of the extract will also be evaluated.

Secondarily, the effect on other parameters related to metabolic syndrome and cardiovascular health will be assessed.

#### 3.2 Endpoints

|                    | Objective                                              | Endpoint                                                                                                                               |
|--------------------|--------------------------------------------------------|----------------------------------------------------------------------------------------------------------------------------------------|
| Primary     | Decrease in blood pressure                             | Systolic blood pressure*                                                                                                               |
| Secondary   | Decrease in blood pressure                             | Systolic blood pressure after 4 weeks*                                                                                                 |
|                    | Decrease in blood pressure                             | Diastolic blood pressure*                                                                                                              |
|                    | Change in markers of oxidative stress                  | oxLDL*, MDA*, GSH*                                                                                                                     |
|                    | Change in lipid profile                                | Total cholesterol*, HDL*, LDL*, non-HDL*, Remnant cholesterol*, Triglycerides*, Apolipoprotein A1*, Apolipoprotein B*, Lipoprotein(a)* |
|                    | Evaluation of side effects                             | Side effects                                                                                                                           |
| Exploratory | Change in parameters linked to metabolic syndrome.     | Fasted glucose*, Hemoglobin A1c*, fasted insulin*, fasted C-peptide*                                                                   |
|                    | Change in parameters linked to metabolic syndrome.     | BMI* en waist circumference*                                                                                                           |
|                    | Change in parameters linked to cardiovascular diseases | Hemoglobin*, Creatinine*, CRP-US*, Homocysteine*                                                                                       |

\* This always refers to the absolute difference compared to the baseline value after 8–9 weeks, unless stated otherwise.

## 4. Trial Design

### 4.1 Description of Trial Design

This is a randomised, placebo-controlled, double-blind study. It includes 56 participants, equally divided into 2 groups (28 participants per group). One group will receive Tensiofytol®, and the other will receive a placebo.

Participation in this study will take a maximum of 10 weeks. The potential participant will be invited for a screening visit. If eligible, the participant will be randomised. The study product will then be delivered to the participant as soon as possible. Intake of the study product must start no later than 1 week after the screening visit. The participant must then take the study product or placebo daily. An interim blood pressure measurement will take place 4 weeks after starting intake. The final visit will be scheduled 8 to a maximum of 9 weeks after starting intake. After the final visit, the participant will be unblinded, marking the end of participation.

Participants will be stratified by sex and then randomised into 2 groups. This will occur 1 to 2 days after the screening visit, once all results are available.

This study is double-blind. The investigators do not know which group the participant is assigned to. The participant will be informed of the treatment they received during the final visit, after all data have been collected. The randomisation list and unblinding at the final visit will be handled by a separate study staff member responsible solely for these tasks.

This is a single-centre study. Participants will be enrolled by researchers from the NatuRAPT research group.

Statistical analysis will be performed after all data from all participants have been collected. No interim analysis is planned.

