### 5.4 Exclusion Criteria

Individuals meeting any of the following criteria will be excluded from participation in this study:

- Age  $< 18$  years or  $> 78$  years
- Smoking
- Triglyceride level  $> 400$  mg/dL
- More than 14 alcoholic drinks per week
- Chronic illness (e.g., diabetes, atherosclerosis, rheumatoid arthritis, ...)
- Acute inflammation
- Pregnancy or intention to become pregnant during the study period
- Breastfeeding
- Regular use of dietary supplements (see §6.8 Concomitant Therapy)
- Use of (chronic) medication (see §6.8 Concomitant Therapy)

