### 6.6.2 Randomisation

Participant numbers will be stratified into two groups by sex and then randomised using an online tool (“Clinical Trial Randomization Tool.” The National Cancer Institute's Division of Cancer Prevention, <https://ctrandomization.cancer.gov>), resulting in two lists of numbers. The aim is to include an equal number of men and women in each group.

Participants will be assigned to these lists in the order of inclusion and thus randomised accordingly.

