## 6.8 Concomitant Therapy

Participants may not use dietary supplements and/or chronic medication.

Participation is possible if the intake of dietary supplements is stopped at least 10 days before the screening visit and throughout the study duration.

For chronic medication use, an individual assessment will determine whether the medication could affect the study endpoints or whether taking the study product is contraindicated.

For example, participation is possible for individuals using antihypertensive drugs if the dosage is stable and will not change during the study. The participant must still meet the inclusion criterion.

Individuals who have been using, for example, a PPI for several months may also participate.

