## 9. Statistical Considerations

### 9.1 Statistical Analysis

Demographic data and baseline values will be used to describe the study groups.

The difference in each parameter compared to baseline will be analyzed using ANCOVA by treatment group, adjusted for baseline values. An  $\alpha$ -level of 0.025 will be applied for the primary analysis. For secondary and exploratory analyses, an  $\alpha$ -level of 0.05 will be used.

The absolute change from baseline in blood pressure over time will be studied using Linear Mixed Models. Baseline value, treatment group, time point, and the interaction between treatment group and time point will be fixed variables. Participant ID will be a random variable.

As sensitivity or exploratory analyses, predictors such as sex, age, baseline values, or compliance may be added to the models to assess whether they have a significant effect.

Subgroup analyses may also be performed, and other continuous parameters can be studied using the same method.

No interim analysis is planned.

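### Stable-dose antihypertensive users may enter, but no model specified in 9.1 contains that status; adding it as a baseline covariate is a cheap improvement, not a correction of an invalid test

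*Protocol*

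**What the plan says.** **Allocation.** Section 4.1: "Participants will be stratified by sex and then randomised into 2 groups". Section 6.6.2 agrees: "Participant numbers will be stratified into two groups by sex and then randomised using an online tool", which gives two lists. No other factor is used.

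**Who may enter.** Section 5.4 lists "Use of (chronic) medication (see §6.8 Concomitant Therapy" among the exclusions and so hands the detail to 6.8. There, for chronic medication, "an individual assessment will determine whether the medication could affect the study endpoints". Antihypertensive users are the first example of people who can pass: "For example, participation is possible for individuals using antihypertensive drugs if the dosage is stable and will not change during the study". A further condition follows: "The participant must still meet the inclusion criterion", that is, a mean SBP of at least 130 mmHg (5.3).

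**Endpoint and models.** The primary endpoint is SBP; the note to the table in 3.2 reads "This always refers to the absolute difference compared to the baseline value after 8–9 weeks, unless stated otherwise". In 9.1 the primary ANCOVA has treatment group and the baseline value. The mixed model for blood pressure has baseline, treatment, time point and treatment by time as fixed terms, with participant as random. For sensitivity or exploratory work, "predictors such as sex, age, baseline values, or compliance may be added to the models", and subgroup analyses are also optional. Antihypertensive use is not named in any of these.

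**The concern.** Treatment status is known before allocation, because 6.8 requires it to be assessed at entry. Baseline SBP may not capture all of it. Two people who both screen at 140 mmHg, one on a stable drug and one on none, could differ in regression to the mean, in adherence to the background drug, or in response to an added product. If so, part of the variance in SBP change belongs to a known factor and stays in the error term, and a chance imbalance in users would move the estimate in that sample.

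The practical stake is interpretation. If the arms turn out unequal, adding the term after the results are seen is a post hoc choice among optional models, and a positive or a negative result could be disputed on that ground.

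This is not a complaint about detail that a statistical analysis plan would normally supply. Section 9.1 itself fixes the terms of both models, and the point concerns those terms.

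**Working it through.** **1. The plan's own figure.** Inputs from 9.2: difference 10.4 mmHg, SD 11.4 mmHg, alpha 0.025, power 80%. The standardised effect is 10.4/11.4 = 0.912. A two-sided two-sample t-test (noncentral t) needs 25 per group, with power 81.6%. Then 25/0.90 = 27.8, so 28 per group and 56 in total. The stated size reproduces.

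**2. Assumptions.** The Protocol gives neither the share of users, p, nor the difference D in SBP change between users and non-users at equal baseline. I take p = 20%, 30% and 40%, and D = 0 to 6 mmHg. The SD of 11.4 is taken as the total residual SD when use is left out of the model.

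**3. Chance of imbalance.** With 28 per arm, 20 points is 0.20 × 28 = 5.6, so a difference of at least 6 users. For two independent Binomial(28, p) counts:

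| p | P(gap of 20 points or more) |
|---|---|
| 0.2 | 6.5% |
| 0.3 | 10.8% |
| 0.4 | 13.3% |

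Fixing the total number of users instead (hypergeometric, 28 v 28) gives 4.0% for 11 users, 8.0% for 17 and 17.1% for 22. The order of size is the same.

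**4. Shift in the estimate.** Shift = gap × D. For a 20-point gap: 0.20 × 2 = 0.4, 0.20 × 4 = 0.8 and 0.20 × 6 = 1.2 mmHg, which is 4%, 8% and 12% of 10.4. The standard error at 25 per group is 11.4 × √(2/25) = 3.22 mmHg, so the shift is at most 1.2/3.22 = 0.37 of a standard error.

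**5. Validity.** In a simulation with 28 per arm, unstratified allocation and 6,000 runs per setting (D = 0, 5, 8; p = 0.2, 0.4), the rejection rate under no treatment effect was 0.022 to 0.028 for the model without the term and likewise with it. The nominal level is 0.025 and the Monte Carlo standard error is about 0.002. Neither model inflates type I error.

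**6. Power with the covariate.** Residual SD = √(11.4² − p(1−p)D²), 25 per group. At p = 0.3 the SD is 11.40, 11.36, 11.25 and 11.06 for D = 0, 2, 4 and 6. Two versions:

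- *Even split of users (47 df):* only the lost degree of freedom counts as a cost.
- *Chance split:* the information is also reduced by the factor 1 − r², where r is the correlation between use and treatment, and power is averaged over two Binomial(25, 0.3) counts. The mean r² is 1/49 = 0.020.

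| D (mmHg) | No covariate | Covariate, even split | Covariate, chance split |
|---|---|---|---|
| 0 | 81.6% | 81.5% | 80.6% |
| 2 | 81.6% | 81.8% | 80.9% |
| 4 | 81.6% | 82.6% | 81.7% |
| 6 | 81.6% | 84.0% | 83.1% |

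So the gain is about 0 to 3 points if users divide evenly, and about one point less on average when their division is left to chance. The simulation agrees: at D = 0 the covariate cost about one point, and at D = 5 it gained about one.

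**The case against.** The case against is substantial and most of it stands.

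- **The Protocol has a safeguard.** Users must be on a constant dose and still reach the SBP threshold. A constant drug acts mainly on the level of SBP, which the baseline term carries. This stands: a residual effect on change is plausible, but nothing in the document shows or quantifies it. A reader might take it as established that antihypertensive use acts on the primary endpoint as analysed; the text does not support that.
- **Use is not shut out of the analysis.** A reader might infer that it can enter no model. The predictor list in 9.1 is introduced by "such as" wording and is optional, so it could be added. What is true is that no specified model contains it.
- **The test is not biased.** A reader might infer bias or an inflated error rate. Randomisation covers chance imbalance, and the standard error already allows for it. The same dispute could be raised over any unstratified factor.
- **Sex-only stratification is not an error.** In 56 people, four short lists would leave more incomplete blocks and could lose part of the balance sought. Section 4.4 also dates the end of recruitment to February 2024.
- **5.4 and 6.8 do not conflict on this point.** The exclusion refers to 6.8 for its detail.

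What survives is narrower. A factor assessed at entry, belonging to a drug class aimed at blood pressure, is absent from the stated models, and deciding to use it only after seeing an imbalance would be weaker than naming it beforehand.

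**Conclusion.** The point holds as a modest improvement to 9.1. The trial may mix treated and untreated people, and the primary ANCOVA and the mixed model do not contain that status. The primary test remains valid, the estimate is unbiased over randomisations, and the allocation scheme is acceptable as it is.

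The size is small: roughly a 6-13% chance of a gap of 20 points or more, moving the estimate by 0.4-1.2 mmHg, well inside one standard error. The power argument alone is weak. At a 30% user share the covariate breaks even at a residual effect near 4 mmHg once chance imbalance is counted. The stronger reason is that a prespecified term removes a later argument about medication imbalance.

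All of this rests on an assumed user share of 20-40% and an assumed residual effect of 0-6 mmHg; the Protocol gives neither. If few users enrol, or the baseline value already captures their difference, the benefit is close to nil.

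**What to change.** In 9.1, before unblinded data are analysed, add baseline antihypertensive use (yes/no) as a fixed covariate in the primary ANCOVA and in the blood pressure mixed models, and report use by arm with the baseline characteristics. If the primary model can no longer be changed, name the adjusted analysis as a prespecified sensitivity analysis. If unblinded results have already been seen, label it post hoc.

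Sections 4.1 and 6.6.2 need no change.

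Cost: one model term built from information assessed at entry, and one degree of freedom. If use has no effect on SBP change, the degree of freedom alone costs about 0.1 point of power, or about one point on average when chance imbalance is included. The gain depends on an effect that the Protocol does not quantify.
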